## Abstract

**Background:**

While the average human life expectancy has increased remarkably, the length of life with chronic conditions has also increased. To limit the occurrence of chronic conditions and comorbidities, it is important to adopt a healthy lifestyle. Within the European project “Council of Coaches,” a personalized coaching platform was developed that supports developing and maintaining a healthy lifestyle.

**Objective:**

The primary aim of this study is to assess the user experience with and the use and potential health effects of a fully working Council of Coaches system implemented in a real-world setting among the target population, specifically older adults or adults with type 2 diabetes mellitus or chronic pain.

**Methods:**

An observational cohort study with a pretest-posttest design will be conducted. The study population will be a dynamic cohort consisting of older adults, aged ≥55 years, as well as adults aged ≥18 years with type 2 diabetes mellitus or chronic pain. Each participant will interact in a fully automated manner with Council of Coaches for 5 to 9 weeks. The primary outcomes are user experience, use of the program, and potential effects (health-related factors). Secondary outcomes include demographics, applicability of the virtual coaches, and user interaction with the virtual coaches.

**Results:**

Recruitment started in December 2019 and is conducted through mass mailing, snowball sampling, and advertisements in newspapers and social media. This study is expected to conclude in August 2020.

**Conclusions:**

The results of this study will either confirm or reject the hypothesis that a group of virtual embodied conversational coaches can keep users engaged over several weeks of interaction and contribute to positive health outcomes.

**Trial Registration:**

The Netherlands Trial Register: NL7911; https://www.trialregister.nl/trial/7911

**International Registered Report Identifier (IRRID):**

PRR1-10.2196/16641

## Introduction

As a result of socioeconomic development and progression in medicine and education, the average human life expectancy has increased significantly [1,2]. However, the aging population has also led to more older adults living with chronic diseases [2,3]. Although these diseases cannot be cured, their burden on patients can be reduced by adopting a healthy lifestyle [2,4,5]. To enable adoption of a healthy lifestyle, a deep understanding of personal motivation and the person’s economic and social pressures is needed [6,7]. Based on these insights, personalized virtual coaching systems have been developed to support lifestyle changes [8]. For these systems, using multiple coaches is more effective than using a single coach because of the potential positive impact of vicarious persuasion as compared with direct persuasion (persuasion of the crowd instead of directly persuading the person) [9]. This insight has led to the introduction of the Council of Coaches (COUCH), a new concept for virtual coaching [10].

COUCH comprises a council of 5-6 virtual coaches. These coaches inform and motivate the user and discuss different topics about healthy living [10]. COUCH was developed in collaboration with end users, and the feasibility and usability of some parts of COUCH have already been tested in a lab setting (formative evaluations). The next step is to gain, through a summative evaluation, knowledge on the possible working mechanism and potential added value of this coaching system in a real-world setting among the target population [11]. As we do not want to interfere with the ongoing development of COUCH, we decided to develop a mature and simplified version of COUCH ready for testing in a real-world setting. This paper outlines the study protocol for this first test in the real world, which aims to evaluate the user experience with and the use and potential health effects of a fully working COUCH system implemented in a real-world setting among the target population.

## Methods

### Trial Design

This study protocol strictly follows the CONSORT-eHEALTH checklist [12] for the introduction and methods sections. This study is an observational cohort study with a pretest-posttest design. It is explorative and evaluative. The participants will be included for at least 5 weeks and up to a maximum of 9 weeks. The first week will consist of the preparation phase. In this phase, baseline measurements will be collected (T0). The following 4 weeks will consist of the implementation phase (T1). The participants will interact with COUCH during this phase. The last 4 weeks will consist of the facultative follow-up phase (T2). Participants can choose whether they want to interact with COUCH for these additional 4 weeks.

This study will be conducted in 2 countries (the Netherlands and Scotland) and consist of 2 rounds. Each round will include 25 participants per country. During the development phase, the technology and content were tested extensively. Therefore, during this study, we do not expect technical problems. However, if participants encounter minor technical problems during the first round, these problems will be fixed. During both rounds, content will be added to various coaches.

To properly evaluate the effectiveness of technology-supported health services, such as COUCH, in the real world is challenging [13-15], and it is currently increasingly acknowledged among experts that there is an urgent need for more pragmatic study designs to adequately evaluate technology-supported health services [13-16]. Microrandomization could be an appropriate alternative study design. The microrandomized trial was introduced by Klasnja et al [17] to overcome the limitations of current experimental methods, for instance randomized controlled trials, and to supplement the use of behavioral theory to guide the development of just-in-time adaptive interventions. As we are also interested in the effectiveness of the interaction between the user and the virtual coaches, we want to assess the applicability of the virtual coaches and the users’ duration of interaction with the virtual coaches of a fully working COUCH system implemented in a real-world setting among the target population. To assess the users’ interaction with the virtual coaches of COUCH, the interaction with one of the primary coaches (physical activity coach) will be microrandomized: Every time the user starts a conversation with this coach, the initiative of starting the conversation will be based on microrandomization. This microrandomization consists of the following two conditions: (1) The user takes the initiative and chooses the topic of the conversation, or (2) the system takes the initiative and automatically suggests the topic of conversation.

The predefined topics include gathering information about the user, goal setting, strategy selection, learning skills, and feedback and support.

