#### Applicability of the Virtual Coaches

The applicability of the virtual coaches will be measured using a rating scale and an adapted version of the Working Alliance Inventory Dutch version for use in the rehabilitation setting. This questionnaire will be completed for the 2 primary virtual coaches. This questionnaire measures how the patient feels about the therapeutic alliance: the better the therapeutic alliance, the more likely the patient will follow the treatment faithfully. Each participant will provide a score between 12 and 60: the higher the score, the more satisfied the participant is with the physical activity or nutrition coach and the more she/he trusts the coach [37].

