### Sample Size

Because of the explorative character of this study, no sample size calculation was conducted beforehand. To answer the objectives of this study, the goal is to include 50 participants per country. So, in each round, 25 participants will be included per country. In our experience, participants are very enthusiastic to participate in this kind of evaluation with new technology before starting the study, but we expect that around 50% of the participants will drop out before the end of the implementation phase.

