### Statistical Analysis

Statistical analyses will be performed using SPSS, version 19 for Windows (IBM Corp, Armonk, NY). For all analyses, the CIs will be set at 95%. Descriptive statistics, such as frequency, mean, SD, and percentages, will be used to describe demographics, user experience, actual use, and the applicability of the coaches.

The outcomes from the EQ-5D-5L, Positive Health questionnaire, and SMAS-S will be investigated using a mixed-model analysis for repeated measures to obtain the effect of using COUCH on the different measurements. The fixed factor will be the measurement time point (T0, T1, or T2). Post hoc comparisons will be conducted when required, and Sidak adjustments will be used to correct for multiple tests.

To assess the users’ interaction with the virtual coaches, the duration of the interaction (in seconds) and the number of dialogue steps with the coach will be used. With this analysis, we want to assess the effect of the conversation with the virtual coaches. To discover changes and possible trends, the duration of the interaction and number of dialogue steps will be analyzed for the two conditions. When the data follow a normal distribution, the outcome will be investigated using a paired *t* test; when the data are not normally distributed, a Wilcoxon signed-rank test will be performed.

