### Limitations

However, this study also has some limitations. First, there will likely be selection bias. Participants contact the researchers to enroll in the study. We expect that these participants are already more motivated to live healthy or already live more healthily than the average older adult population and the average adult population with type 2 diabetes or chronic pain. Second, the content that will be ready at the start of the evaluation only lasts for 4 weeks. During the follow-up phase, no new content will be provided to the participants. This can influence the interaction frequency during the follow-up phase. Finally, this study will possibly have to deal with confounders, for example if users receive advice from their health care professionals or others about a healthy lifestyle. This occurs in real life. To handle this as best as possible, confounders such as these will be discussed with the users during the exit interview.

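### Health outcomes from two countries and two rounds, with content added during both rounds, are modelled with time point as the only fixed factor, although about half the participants are expected to drop out

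*Protocol article*

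**What the plan says.** The Trial Design section of the Protocol article states: "This study will be conducted in 2 countries (the Netherlands and Scotland) and consist of 2 rounds". It adds "Each round will include 25 participants per country", and the Sample Size section gives the matching total: "the goal is to include 50 participants per country".

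The system is not held constant. Trial Design says "During both rounds, content will be added to various coaches". Technical repairs are conditional: "if participants encounter minor technical problems during the first round, these problems will be fixed", and the same section says that technical problems are not expected.

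The Statistical Analysis section analyses the EQ-5D-5L, Positive Health and SMAS-S with a mixed model for repeated measures: "The fixed factor will be the measurement time point (T0, T1, or T2)". Country, round and content version are not mentioned there. User experience, use and coach applicability are to be summarised descriptively, with no split named.

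The Sample Size section expects about half the participants to leave before the implementation phase ends. On content, the Limitations section says: "During the follow-up phase, no new content will be provided to the participants".

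**The concern.** A likelihood-based mixed model copes with dropout when the missingness depends only on what is in the model: the earlier responses and the fixed factors. Country and round are design variables known for every participant, and both dropout and outcome could plausibly depend on them. Left out, they cannot do that work. The time effect is then pulled towards whichever round or country keeps more of its participants.

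The outcomes measured only at T1 (the Technology Acceptance Model constructs, the System Usability Scale, willingness to pay and the Working Alliance Inventory) have no model behind them. Their pooled summaries simply follow the mix of people still present.

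There is also a plain reporting gap. Content changes by design, the rounds are run at different times and the sites are in different countries. As written, the analysis cannot show whether results were alike across these parts or whether the pooled figure averages unlike ones.

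**Working it through.** **Inputs from the Protocol article.** 25 participants per country per round; 2 countries; 2 rounds; about 50% dropout before T1; 95% confidence intervals; time point as the only fixed factor.

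**Assumed inputs, because the article gives none.** Dropout by round of 50%/50%, 60%/40% or 70%/30% (each 50% overall); outcome SD of 1 at each visit; T0–T1 correlation of 0.6; a baseline difference between rounds of 0 or 0.5 SD; true mean change of 0.20 SD, either equal in both rounds or 0 in round 1 and 0.4 SD in round 2. The arithmetic is the same with country in place of round.

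**1. The plan's own figure.** 25 × 2 rounds = 50 per country, and 50 × 2 countries = 100, as stated. At 50% dropout there are 50 completers at T1: 25 per round or per country, and 12.5 per country-by-round cell.

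**2. Unequal dropout with unequal change.** At 70%/30% dropout, round 1 keeps 50 × 0.3 = 15 and round 2 keeps 50 × 0.7 = 35. With equal baselines the time-only estimate is the completer-weighted change: (15 × 0 + 35 × 0.4)/50 = 0.28 SD, against 0.20 SD for those enrolled. At 60%/40% it is (20 × 0 + 30 × 0.4)/50 = 0.24. If the 70% dropout falls in round 2 instead, it is (35 × 0 + 15 × 0.4)/50 = 0.12. The direction therefore depends on which round loses more people.

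**3. Unequal dropout with unequal baseline, equal change of 0.20.** Let round 2 start 0.5 SD higher and have 30% dropout.
- Mean T0 of all enrolled: 0.5 × 0.5 = 0.25. Mean T0 of completers: 0.7 × 0.5 = 0.35. Mean T1 of completers: 0.35 + 0.20 = 0.55.
- Slope of T1 on T0 among completers: (0.6 + 0.25 × 0.21)/(1 + 0.25 × 0.21) = 0.6525/1.0525 = 0.62, where 0.21 = 0.7 × 0.3.
- Estimated T1 mean: 0.55 − 0.62 × (0.35 − 0.25) = 0.488. Estimated change: 0.488 − 0.25 = 0.238, or about 0.24 SD.

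The model's use of baseline values removes part of the distortion, but not all of it.

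**4. Simulation of the same cases** (4,000 repetitions, 50 enrolled per round; true mean change 0.20 throughout):

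| Dropout, round 1/2 | Change, round 1/2 | Baseline difference | Time only | Round × time, equal weights |
|---|---|---|---|---|
| 50%/50% | 0.2/0.2 | 0 | 0.203 | 0.203 |
| 60%/40% | 0.2/0.2 | 0 | 0.203 | 0.203 |
| 60%/40% | 0.2/0.2 | 0.5 | 0.218 | 0.200 |
| 70%/30% | 0.2/0.2 | 0.5 | 0.239 | 0.201 |
| 50%/50% | 0/0.4 | 0 | 0.197 | 0.198 |
| 60%/40% | 0/0.4 | 0 | 0.240 | 0.199 |
| 70%/30% | 0/0.4 | 0 | 0.281 | 0.201 |
| 70%/30% | 0/0.4 | 0.5 | 0.315 | 0.202 |

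Unequal dropout alone does no harm (second row). Nor does a difference in change alone (fifth row).

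**5. Scale of the bias.** The 95% half-width for a mean change is 1.96/√n: 0.28 SD of change with 50 completers, 0.39 with 25 and 0.55 with 12.5. With correlation 0.6 the SD of change is √(2 × 0.4) = 0.894 outcome SD, so 0.277 × 0.894 = 0.25 outcome SD for 50 completers. A bias of 0.04 to 0.08 is 0.04/0.25 = 16% to 0.08/0.25 = 32% of that half-width.

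**6. What the interaction can show.** With 25 against 25 completers the standard error of a difference in change is √(2/25) = 0.283 SD of change. For a difference of 0.5 the power is Φ(0.5/0.283 − 1.96) = 42%; for 0.3 it is 18% and for 0.8 it is 81%. The smallest difference detectable with 80% power is 2.80 × 0.283 = 0.79.

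**7. T1-only descriptives.** With 70%/30% dropout the completers are 35 and 15, so pooled T1 summaries are weighted 70:30 although enrolment was 50:50.

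**The case against.** The strongest reply is that no bias has been shown. The article gives one overall dropout figure, not one per round or country, and does not say that baseline or change differs. The mixed model keeps the baseline values of those who leave, which limits the distortion, and the resulting bias is small beside the confidence interval. The study is explorative, and tables by site and round are ordinary analysis-plan detail. All of this is fair, and it limits the point to a risk. What it does not answer is that the article states the model's fixed factor outright, so the omission of country and round is more than a detail left for later.

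Several stronger readings are tempting and are not supported:
- **That round 1 tests a faulty system later repaired.** Repairs are conditional, minor and not expected. Only the content additions are certain.
- **That Trial Design and Limitations contradict each other on content.** Content could be added in a round's implementation weeks and withheld from those in follow-up. The article does not say how releases are timed, so this is an ambiguity.
- **That the Euro question and the "adapted version of the Working Alliance Inventory Dutch version for use in the rehabilitation setting" undermine the model.** Both are measured at T1 only and never enter it. The survey wording is in an appendix not shown.
- **That inclusion group must also be a fixed factor.** The groups overlap: a person of 55 or over with diabetes belongs to two.
- **That the microrandomised comparison needs round or version terms.** It is made within person, and condition is assigned at each conversation.
- **That comparing versions is a neglected aim.** The stated objective does not include it.

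**Conclusion.** The concern holds as a risk that the stated model leaves open and that is cheap to close. Bias requires two things together: dropout that differs by round or country, and a baseline level or change that differs along the same line. Under the assumed 70%/30% dropout, 0.20 SD becomes about 0.24 or 0.28 SD, and about 0.32 SD if both differences are present. With equal levels and equal change it stays at 0.20. These sizes rest on the assumed dropout split, correlation and differences; the article supplies only the 50% overall.

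The second part of the conclusion needs no assumption: with time as the only factor, the planned analysis of the health outcomes cannot show whether results differ between rounds or countries, although the design guarantees that content changes during the study.

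**What to change.** - Add country and round as fixed factors in the mixed model, with time × round and time × country as terms labelled exploratory. The main effects address differences in level; the interactions are needed where change differs.
- Report change by round and by country with 95% confidence intervals, and an overall change that weights rounds and countries equally, as enrolment does.
- Report dropout, user experience, use and coach applicability by country and round as well as pooled.
- Record the date of each content release and of any technical repair. Content is added within rounds and the calendar period differs between them, so a round term captures version only in part.
- State how content added during both rounds fits with the statement that none is provided in follow-up.

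The model terms and tables use variables already held for every participant, so the cost is small; the release log is the only new record. The price is imprecision: with about 25 against 25 completers, power is roughly 42% for a difference of 0.5 SD of change. The interaction results should be read as estimates with intervals, and a non-significant interaction should not be taken as evidence that rounds or countries are alike.

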### Participants

The study population will consist of older adults and adults with type 2 diabetes mellitus or chronic pain. For this study, the term older adult is defined as ≥55 years of age, and adult is defined as ≥18 years of age. A potential participant who meets any of the following criteria will be excluded from participating in this study: not able to read and speak Dutch or English, not having a Wi-Fi connection at home, not able to provide informed consent, or not able to see the smartphone or tablet screen clearly.

Eligible older adults will be recruited for the first round from December 2019 through January 2020. Participants will be recruited for the second round from March through April 2020. The first round will start in February 2020. The preparation phase (1 week) will start with an initial visit to the participant’s home or an intake at the researcher’s lab. During this phase, the participants do not interact with COUCH yet, but they will wear sensors for the baseline measurements, and they can keep track of their eating patterns using a food diary. The needed equipment (eg, tablet, smartphone, sensors) will be provided to the participants during this first visit, and they will receive an explanation about the operation of any equipment. Finally, participants will complete the T0 questionnaire. After this first week, the implementation phase will start. The participants will start using the COUCH system for 4 weeks. Thereafter, the second visit will take place at home or at the research location. During this visit, an exit interview will be conducted. The participants will complete the T1 questionnaire, and they will choose whether they want to continue using COUCH for another 4 weeks (the facultative follow-up phase). If they do not want to keep using COUCH, they will return the borrowed equipment to the research staff. After the follow-up phase, all participants will complete the T2 questionnaire. The questionnaires (online or on paper) will be filled in at T0, T1, and T2 (see Figure 1).

**Figure 1 figure1:**
[figure not shown]
Study procedures for the first and second rounds of this 9-week observational study with a pretest-posttest design.

### Intervention

The application is a web application, designed and built to run on tablets or computers. This technology is currently under development within the COUCH project (European Union’s Horizon 2020 research and innovation program under grant agreement No. 769553). The application’s main functionality is to provide a friendly and easy-to-use interface that allows users to have natural language dialogues with a group of (5-6) virtual coaches (see Figures 2 and 3). The final COUCH demonstrator will support the following virtual coaches: physical activity, nutrition, social, cognition, peer/support, chronic pain, and diabetes. Depending on the user’s needs and interests, a subset of these coaches can be selected by the user (eg, in the absence of the specific conditions, the chronic pain and diabetes coaches will not be presented to the user).

**Figure 2 figure2:**
[figure not shown]
Screenshot of the current test version of the Council of Coaches web application with the chronic pain coach, without a dialogue box (https://www.council-of-coaches.eu/beta/).

**Figure 3 figure3:**
[figure not shown]
Screenshot of the current test version of the Council of Coaches web application with the chronic pain coach, with a dialogue box (https://www.council-of-coaches.eu/beta/).

The content provided by the virtual coaches focuses on physical fitness and nutrition to improve the users’ wellbeing, and the content is based on (Dutch) health guidelines. Both the physical activity and nutrition coaches, which are the primary coaches, can assist the user in their domain in the following ways: providing information on health benefits, setting personalized goals, providing feedback and advice, reflecting on different coaching styles, and assisting with relevant sensor technology.

The secondary coaches (social, cognition, peer/support, chronic pain, and diabetes) interact with the user by providing their points of view on the main topics of activity and nutrition. For example, the social coach may suggest doing group activities outside the house when the user is discussing physical activity with his physical activity coach, while the cognitive coach can provide a memory game to do while grocery shopping for a recipe that the nutrition coach recommended. The peer/support coach is included to be “on the side of the user” and provides encouragement for the user to achieve his/her goals. The secondary coaches, except for the chronic pain and diabetes coaches, can be removed from the council by the user. The interaction with the physical activity coach will be microrandomized [17]. Every time the user starts a conversation with a primary coach, the initiative of the conversation will be taken by the system or given to the user.

The application optionally supports the use of sensor technology, in order to allow personalized feedback and coaching to the users. The physical activity coach will suggest the user wears a Fitbit watch, which is provided by the researchers to all participants, so that she may provide feedback on the user’s actual activity. Similarly, the nutrition coach will ask the user to track dietary consumption through a provided smartphone app and ask the user to enter their weight information either manually or through a connected (smart) scale. Users can talk with their virtual coaches about the use of these devices, and the coaches will explain which data is collected and for what purpose and offer the ability to stop tracking data when the user feels uncomfortable about this.

All of the interactions take place in the comfort of the coaches’ living room (see Figure 2) that includes elements like a radio (playing the coaches’ favorite classical songs), recipe books (that Francois, the nutrition coach, can guide the user through), and a television on which to watch physical exercise examples.

During the first visit (T0), the participants will be trained by the researcher to learn how to interact with COUCH on their tablet, and they will receive a paper manual about COUCH. During the entire evaluation period, there will be a helpdesk available for the participants on working days from 9 am to 5 pm, and the participants will receive a nonpersonalized informative newsletter three times by email to inform them about the project and running evaluation.

